## Abstract

**Background:**

Pneumonia is a leading cause of death among children under 5 specifically in South Asia and sub-Saharan Africa. Hypoxaemia is a life-threatening complication among children under 5 with pneumonia. Hypoxaemia increases risk of mortality by 4.3 times in children with pneumonia than those without hypoxaemia. Prevalence of hypoxaemia varies with geography, altitude and severity (9%–39% Asia, 3%–10% African countries). In this protocol paper, we describe research methods for assessing impact of Lady Health Workers (LHWs) identifying hypoxaemia in children with signs of pneumonia during household visits on acceptance of hospital referral in district Jamshoro, Sindh.

**Methods and analysis:**

A cluster randomised controlled trial using pulse oximetry as intervention for children with severe pneumonia will be conducted in community settings. Children aged 0–59 months with signs of severe pneumonia will be recruited by LHWs during routine visits in both intervention and control arms after consent. Severe pneumonia will be defined as fast breathing and/or chest in-drawing, and, one or more danger sign and/or hypoxaemia (Sa02 <92%) in PO (intervention) group and fast breathing and/or chest in-drawing and one or more danger sign in clinical signs (control) group. Recruits in both groups will receive a stat dose of oral amoxicillin and referral to designated tertiary health facility. Analysis of variance will be used to compare baseline referral acceptance in both groups with that at end of study.

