**Trial registration number:**

NCT03588377.

Strengths and limitations of this studyOur study will directly assess impact of pulse oximetry on family referral acceptance by comparing family acceptance of hospital referral (verbal acceptance with hospital visit) in ‘pulse oximetry and clinical signs’ group with ‘clinical signs alone’ group.The study has applicability because it assesses impact with ‘real-life’ limitations (variability in lady health worker accuracy in identifying severe pneumonia, availability of oxygen and human resource at referral hospital and, availability of private transportation).The study design provides means of minimising the effect of confounding.The study design avoids bias in allocation to exposure groups.Blinding is not possible due to nature of intervention.Some subjects may fail to adhere to protocol and non-adherence may cause an underestimated measure of association.

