**Figure 1 F1:**
[figure not shown]
Trial profile. LHW, Lady Health Worker, PO, Pulse Oximetry.

The primary outcome is hospital referral acceptance in children under 5 with severe pneumonia and to identify demographic and clinical predictors of hospital referral acceptance. The predictors will include distance of child home to referral facility, socioeconomic status of household, parental education, child age, nutritional status, respiratory rate, temperature, hypoxaemia and presence of other illnesses.

Secondary outcomes include duration of oxygen therapy, treatment failure, duration of hospital stay, vital and health status of child at day 7th and 14th.

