**Figure 2 F2:**
[figure not shown]
Map of intervention and control sites Abbreviations used in Map: Liaqat University of Medical and Health Sciences Jamshoro (LUMHS). Legend: Lady Health Worker (LHW). Service Layer Credits: Companies/institutes which contributed and collaborated to make this basemap publicly available (Environmental Systems Research Institute (ESRI), HERE (private company), General Bathymetric Chart of the Oceans (GEBCO), US Geological Survey (USGS), Food and Agriculture (FAO), National Park Service (NPS), National Resources Canada (NRCan), GeoBase, Institut Geographique National (IGN), Ministry of Economy, Trade and Industry (METI).

Participants will be the permanent residents of Kotri, Jamshoro and recruited from their homes during routine monthly visits by LHWs serving in their catchment areas. This study is expected to run for 48 months with participant identification and enrolment conducted simultaneously in intervention and control clusters over 21 months after an initial pilot of 1 month. Each enrolled child will be revisited at day 7 and 14 for outcome measurement.

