### Randomisation and masking

Study clusters were defined as the area covered by an LHW. Each LHW covers a minimum of 100 households. A list of LHWs working in Kotri was collected from the LHW programme, health department government of Sindh. There are a total of 188 active LHWs in the study site. A baseline survey was conducted to collect data on health indicators from the LHW catchments. The clusters were randomly allocated to intervention and control groups on 1:1 fashion with a computer-generated randomisation sequence that was generated by an independent expert. Clusters were matched on under 5 population and distance to referral health facility. No stratification was used for allocation; clusters were selected to ensure that the reporting and training centres of intervention and control LHWs were separate. The investigators and the national and provincial LHW programme coordinators will be excluded from the allocation process.

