### Data analysis

The primary analysis for each outcome will perform on an ‘intention-to-treat’ basis, that is, all children included in the analysis who were enrolled in the study according to the group to which they were allocated. All analyses will account for the cluster randomised design to ensure correct type I error rates and CIs.^35^ Baseline characteristics will be compared by analysing differences in means and proportions among the study arms. Categorical outcomes will be compared using χ^2^ test and continuous outcomes using Student’s t-test. For analysis of predictors of referral acceptance, generalised linear model will be used with logit link function. The univariate analysis will be conducted to explore the independent effect of each predictor on outcome. The variables significant at a liberal p<0.20 will be included in multivariate model for adjustment. The results will be reported as relative risk with 95% CI. Type 1 error will be set at 5% level. All analysis will be done using STATA V.15.

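### The abstract's baseline-to-end ANOVA conflicts with the between-arm comparison in the methods, and the tests named there are not stated in cluster-adjusted form

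*Protocol article*

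**What the plan says.** **Abstract, Methods and analysis.** "Analysis of variance will be used to compare baseline referral acceptance in both groups with that at end of study". It names no other analysis.

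**Strengths and limitations box; Study aims and design.** The box describes the study as "comparing family acceptance of hospital referral (verbal acceptance with hospital visit") in the pulse oximetry arm with that in the clinical signs arm. The first primary objective is likewise a contrast of intervention with non-intervention clusters. "The primary outcome is hospital referral acceptance in children under 5 with severe pneumonia", which is a yes/no outcome for each child.

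**Data analysis.** The primary analysis is by intention to treat according to allocated group. "All analyses will account for the cluster randomised design to ensure correct type I error rates and CIs". Then: "Categorical outcomes will be compared using χ^2^ test and continuous outcomes using Student’s t-test". A generalised linear model with logit link is named for the predictors of acceptance, with variables entering the multivariable model if p<0.20 in univariate analysis. Neither ANOVA nor a baseline-to-end contrast is mentioned.

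**Trial setting; Randomisation and masking.** A baseline survey gathered health indicators from the LHW catchments. The results reported concern birth attendance, antenatal and postnatal care, vaccination and care seeking. After a one-month pilot, the article plans "enrolment conducted simultaneously in intervention and control clusters over 21 months". On allocation: "Clusters were matched on under 5 population and distance to referral health facility".

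**The concern.** A reader who wants to know how the trial will be judged finds two answers. The abstract points to change over time, and the methods point to a difference between arms. Randomisation protects only the second. A change from baseline to end of study would also pick up season, the disruption of field work in 2020 and the LHWs' growing experience. The trial is unblinded and recruiting, so leaving two analyses on record also leaves room to choose between them after the data are seen.

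The second worry is the error rate. The LHW persuades the family, so acceptance may well vary by LHW. A chi-square or t-test run on individual children without adjustment would then give p-values that are too small and intervals that are too narrow.

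The third is smaller. Under-5 population and distance to the facility were important enough to match on, yet the article does not say that the arm comparison will use either.

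**Working it through.** **1. Which comparison?**

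| Place | Contrast | Method |
|---|---|---|
| Abstract | Baseline v end of study, in both groups | ANOVA |
| Strengths and limitations box | Arm v arm | none named |
| Study aims and design | Arm v arm | none named |
| Data analysis | By allocated group | Chi-square, t-test; logit GLM for predictors |

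Only the abstract has a time contrast.

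**2. Are there data for the abstract's analysis?** Three places could supply a baseline.
- The baseline survey: referral acceptance is not among the indicators reported.
- The enrolment schedule: both arms enrol at the same time, and no enrolment period before the intervention is described. A child enters only on meeting the referral criteria, so there is no earlier acceptance value for that child.
- The Sample size section: its 10% baseline is a planning assumption for the power calculation.

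None of these describes a measurement of baseline acceptance.

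**3. What would unadjusted tests cost?**

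Inputs: total 4160 and ICC 0.001736 (Sample size); alpha 5% (Data analysis), taken as two-sided because sidedness is not stated. The number of clusters randomised is not stated. I assume the 188 active LHWs given under Randomisation and masking.

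The plan's own figure comes first, because it sets the cluster size. For 10% v 15%, 90% power and two-sided 5%, the usual pooled formula gives 918 per arm, or 1836 in total. With the design effect below, this becomes 1836 × 1.0367 = 1903. The stated 4160 is not reproduced. That is a separate matter, and I use 4160 here only as the planned enrolment.

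- Children per cluster: m = 4160/188 = 22.13
- Design effect: DE = 1 + (m − 1) × ICC = 1 + 21.13 × 0.001736 = 1.0367
- True type I error of an unadjusted test: 2 × [1 − Φ(1.96/√DE)] = 2 × [1 − Φ(1.925)] = 0.054

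Only the first ICC below is in the article; the others are assumptions. The 94-cluster column (m = 44.26) shows what happens if half as many clusters took part.

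| ICC | DE, 188 clusters | Type I error | DE, 94 clusters | Type I error |
|---|---|---|---|---|
| 0.001736 (stated) | 1.037 | 5.4% | 1.075 | 5.9% |
| 0.01 (assumed) | 1.211 | 7.5% | 1.433 | 10.2% |
| 0.02 (assumed) | 1.423 | 10.0% | 1.865 | 15.1% |

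**4. Where do the matching factors appear?** Distance from the child's home to the referral facility is a listed predictor (Study aims and design). It therefore reaches the predictor model, but stays in the multivariable version only if it passes the p<0.20 screen. Under-5 population of the cluster is not listed. Neither is fixed in the between-arm comparison.

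**The case against.** The strongest reply concerns the Data analysis section. A reader might infer that the trial will run plain tests that ignore clustering, and that its primary analysis is therefore invalid. The text does not support that. The section commits all analyses to the cluster design, and cluster-adjusted chi-square tests and t-tests on cluster summaries are standard. The two sentences can be read together, and the choice of adjustment may sit in a fuller document. This stands. What remains is that the tests are named in a form that, taken literally, does not deliver the commitment. The t-test, moreover, is for continuous outcomes and so is not an analysis of the binary primary outcome.

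On the ANOVA, it can be said that the abstract does not call it primary, that ANOVA on cluster-level proportions is a recognised method, and that the full protocol may hold baseline acceptance data. All fair. It would be wrong to say that no such data exist or that the analysis is impossible; the supportable statement is that none are described. None of this reconciles the abstract's time contrast with the between-arm comparison.

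On size, one could back-solve from 4160 an ICC near 0.06 and report a type I error of about 19%. That attributes an unexplained sample size wholly to clustering and contradicts the stated ICC, so I do not rely on it.

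Lastly, it would be wrong to say that the matching factors are absent from the analysis, because distance is a listed predictor.

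**Conclusion.** The point holds in a limited form. The firm part is the contradiction: the abstract announces a before/after ANOVA, the methods describe a concurrent randomised comparison, and no baseline acceptance measurement is described. This needs no numerical assumption.

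The part on the named tests is an ambiguity with a bounded cost. If they were applied without adjustment, the type I error would be about 5.4% instead of 5% at the stated ICC, assuming 188 clusters of about 22 children, equal cluster sizes and a two-sided test. It grows if the true ICC is larger (about 7.5% at an assumed 0.01) or if fewer clusters take part. That is a reason to state the adjustment, and not evidence that the planned analysis is invalid.

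The matching factors are a lesser gap: neither is fixed in the arm comparison, and distance depends on a significance screen.

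**What to change.** 1. Delete the ANOVA sentence from the abstract.
2. State one primary analysis: the between-arm comparison of referral acceptance by a named cluster-adjusted method. A log-link GEE with cluster-robust standard errors would give the relative risk that the article says it will report; a cluster-adjusted chi-square test is an acceptable alternative.
3. For continuous outcomes, name the cluster-adjusted analogue of the t-test.
4. Include under-5 population and distance to the referral facility as prespecified covariates in the between-arm model, whatever the p<0.20 screen shows. If the cluster-adjusted chi-square is chosen, give the covariate-adjusted result from a model alongside it.

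The cost is a few sentences, standard Stata code and slightly wider intervals: at the stated ICC with 188 clusters, by a factor of about √1.0367 = 1.018 compared with unadjusted ones. The matching was done on the two factors, so no new data collection should be needed.

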**Ethics and dissemination:**

Ethical approval was granted by the Ethics Review Committee of the Aga Khan University (4722-Ped-ERC-17), Karachi. Study results will be shared with relevant government and non-governmental organisations, presented at national and international research conferences and published in international peer-reviewed scientific journals.

**Trial registration number:**

NCT03588377.

Strengths and limitations of this studyOur study will directly assess impact of pulse oximetry on family referral acceptance by comparing family acceptance of hospital referral (verbal acceptance with hospital visit) in ‘pulse oximetry and clinical signs’ group with ‘clinical signs alone’ group.The study has applicability because it assesses impact with ‘real-life’ limitations (variability in lady health worker accuracy in identifying severe pneumonia, availability of oxygen and human resource at referral hospital and, availability of private transportation).The study design provides means of minimising the effect of confounding.The study design avoids bias in allocation to exposure groups.Blinding is not possible due to nature of intervention.Some subjects may fail to adhere to protocol and non-adherence may cause an underestimated measure of association.

## Introduction

Pneumonia accounts for an estimated 18% of under 5 mortality across the globe.^1^ Majority of these pneumonia-specific deaths occur in 15 countries, in which Pakistan ranks fifth.^2^ Failure to seek early care and delays in hospital referral are commonly acknowledged determinants of mortality in childhood pneumonia with a higher proportion reported from rural settings than urban.^3–6^ Acceptance rates of ‘facilitated’ hospital referral advice have been reported low between 8% and 23% for sick young infants in periurban Karachi.^7 8^ They are even lower for non-facilitated referral in rural settings in children under 5 with severe pneumonia in rural Matiari district, Sindh.^5^ The prominent reasons in low-income and middle-income countries behind this delay are inability to recognise seriousness of pneumonia, distance from health facility and lack of money for private healthcare.^9 10^

In 1994, the government of Pakistan introduced the Lady Health Worker (LHW) programme in rural populations with low physician density to address common health problems in women and children under 5 through household visits. To date, a team of over 110 000 LHWs are working for the programme nationwide with 23 185 LHWs in Sindh alone.^11^ Each LHW is responsible for a population of 1000–1500 individuals (catchment of about 100 families). Recruits are preferably local, with a minimum of 8 years of formal schooling, followed by 15 months of training to deliver maternal and child healthcare (MCH) in community settings. During a monthly home visit, the LHW provides essential MCH services including family planning needs, nutritional assessments of both mother and child, management of minor and common illnesses, improving immunisation coverage and imparting health education.^12^

This study recognises the LHW as a powerful conduit for reaching under 5 children at household level and identifying severe pneumonia in under five at an early stage. It also recognises the underestimation of hypoxaemia (arterial oxygen saturation, SpO_2_ of <90%), a major risk factor for pneumonia mortality at community level and assesses its prevalence. The reported prevalence of hypoxaemia in under 5 acutely ill children is 5%–58% in facilities^13–16^ and 16%–39% in community settings.^17^ A 4.3-time higher risk of mortality has been associated with pneumonia with hypoxaemia than in children with pneumonia without hypoxaemia.^13^ Hypoxaemia is also predictive of treatment failure with amoxicillin in children aged 3–59 months.^18^ In resource-poor settings where pulse oximetry is not feasible, signs and symptoms of severe pneumonia (sleepiness, cyanosis, head nodding/grunting and inability to move) are used as predictors of hypoxaemia. However, the validity of clinical signs to predict hypoxaemia varies and it is often difficult for physicians working in settings, where objective detection of hypoxaemia is not available, to decide whether the child coming with severe pneumonia requires administration of oxygen or not.^15 19 20^

Pulse oximetry^16^ is a rapid, portable, non-invasive and accurate method of measuring Sp02 and has therefore been used in trial and clinical settings to detect hypoxaemia. Appropriate oxygen therapy (based on PO findings rather than clinical signs of severity alone) has been associated with lower mortality risk.^19^ Assuming access to supplemental oxygen, PO could potentially avert up to 148 000 severe pneumonia-related deaths if implemented, and, combining PO with IMCI assessment for pneumonia has been shown to be cost-effective in 15 high burden countries.^21^ Emdin *et al* found first level LHWs in periurban Karachi could easily perform pulse oximetry on young infants on well and sick visits to a primary healthcare facility.^22^

Over the past decade, the possible impact of pulse oximetry in hospital and community settings has been of interest across the globe. Health survey of 54 countries in 2010, suggested that 19.2% of the operating theatres around the globe are not equipped with pulse oximeters.^23^ Trials assessing utility of pulse oximetry on a health systems level in Nigeria have shown that health workers reserve PO for the sickest patients.^24 25^ This has also been observed in areas at higher altitudes with higher prevalence of hypoxaemia (highlands of Papua New Guinea).^25 26^ There is lack of clarity about how pulse oximetry can be used in the community where lower hypoxaemia prevalence may be a lesser incentive for health workers to use PO such as in interior Sindh settings in Pakistan. Then again, health workers recruited from within communities may be better invested and motivated than hospital personnel in following case management guidelines precluding PO. It is, therefore, worthwhile to explore and describe contexts behind a family’s acceptance (or not) of referral advice whether based on technology and/or clinical examination in rural settings where the highest burden of pneumonia deaths lies.

Feasibility and sustainability audits of oxygen delivery systems in the Gambia and Egypt have shown that providing technology alone is ineffective, and should preclude provision of supplies, education, training and feedback.^27–30^ This protocol paper describes a study to assess the effect of PO monitoring in community settings on hospital referral acceptance in children under 5 with severe pneumonia.

## Methods

### Study aims and design

The overall aim of the study is to assess if detection of hypoxaemia, and/or severe pneumonia in children 0–59 months by LHWs during their monthly home visits will increase hospital referral acceptance among families in district Jamshoro, Sindh, Pakistan.

Primary objectives are:

To assess and compare the impact of ‘pulse oximetry’ used by LHWs at household level on increasing hospital referral acceptance rates in intervention clusters (district Jamshoro) for children aged 0–59 months with severe pneumonia with the impact of LHWs using clinical signs alone in non-intervention clusters of the same district.To investigate the likely predictors (demographic, clinical) of hospital referral acceptance in both the groups.

Secondary objective is:

To compare clinical outcomes (treatment completion, treatment failure, hypoxaemia) of children 0–59 months who accepted referral to those who refused admission and were treated at home.

A community-based cluster randomised trial will be conducted in district Jamshoro, among children of ages 0–59 months (figure 1). In intervention areas, all children with cough, fever or difficulty in breathing (acute respiratory illness) will be assessed for study eligibility (signs and symptoms of severe pneumonia, or hypoxaemia alone, or severe pneumonia with hypoxaemia) by LHWs during their monthly home visit in their catchment area. In control areas, study eligibility will require detection of signs of severe pneumonia alone (online supplemental appendix 1) during LHW monthly visits. Data will be collected on demographics, likely predictors and clinical outcomes using a structured questionnaire.

10.1136/bmjopen-2020-046158.supp1Supplementary data

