### Limitations

Some union councils with poor LHW coverage were not included in this study. This was a compromise on generalisability in favour of feasibility. It may have led to exclusion of children whose referral patterns were important to gauge. We also did not offer facilitated referral in either arm. This may have affected referral acceptance in both groups, however, will allow assessment of real-life impact of transportation barriers.

Though we kept hospital referral (as recommended by WHO) for severe pneumonia as our standard of care, it was beyond the scope of this study to ensure that referral centres had sustainable oxygen systems/capacity for non-invasive ventilation in children with severe pneumonia, or readily available cardiac evaluation resources for children with hypoxaemia alone. Duke *et al* showed improved case fatality rates by providing oxygen concentrators and pulse oximeters at five hospitals in PNG along with protocols for use.^35^ Lack of quality care at referral hospitals in developing countries is a recognised barrier to healthcare seeking behaviour.^40 41^

If our study reveals pulse oximetry has influenced health-seeking behaviour significantly, we will need to follow with a more systematic evaluation of pneumonia care at rural hospitals which vary in quality of care. We will also need to correlate recovery rates in those who accepted hospital referral versus those who stayed home on oral amoxicillin. Evidence to support home care for severe pneumonia is poor.^42^

The COVID-19 pandemic has adversely affected recruitment in the study with disruption of field activities for many months in 2020. We anticipate prolongation of study duration in order to achieve sample size.

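### The acceptor-versus-refuser comparison of clinical outcomes is a self-selected contrast, and the stated tests make no adjustment for severity or access

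*Protocol article*

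**What the plan says.** The secondary objective (Protocol article, Study aims and design) compares three clinical outcomes, namely treatment completion, treatment failure and hypoxaemia, between children "who accepted referral to those who refused admission and were treated at home".

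The Data analysis section contains four statements that bear on this:

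- The primary analysis of each outcome takes children "according to the group to which they were allocated".
- The general adjustment concerns clustering: "All analyses will account for the cluster randomised design to ensure correct type I error rates and CIs".
- The tests named for outcomes are simple ones: "Categorical outcomes will be compared using χ^2^ test and continuous outcomes using Student’s t-test".
- The one regression described has a different response: "For analysis of predictors of referral acceptance, generalised linear model will be used with logit link function". The p<0.20 screening rule and the multivariable step follow from this sentence.

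The candidate predictors of acceptance, listed after the trial profile figure, include distance to the facility, socioeconomic status, parental education, child age and nutritional status, together with "respiratory rate, temperature, hypoxaemia and presence of other illnesses". The Introduction reports a 4.3-fold mortality risk with hypoxaemia. It also says that hypoxaemia predicts amoxicillin treatment failure at 3 to 59 months, without giving a size.

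**The concern.** Randomisation protects the comparison of intervention with control clusters. It gives no protection to a comparison of families who went to hospital with families who did not. If a variable influences both the decision and the child's outcome, the crude difference mixes the effect of hospital care with that variable. The protocol names such variables on both sides. Hypoxaemia is a candidate predictor of acceptance and a reported predictor of outcome. Distance, wealth and education are candidate predictors of acceptance and may plausibly affect outcome as well.

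Allowing for clustering corrects standard errors but does not remove this bias, and the one adjusted model has acceptance, not clinical outcome, as its response. What is at stake is how the contrast reads. Anyone comparing hospital with home care for severe pneumonia could take a crude ratio as an effect of care when it partly reflects who was taken to hospital.

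**Working it through.** The plan gives no figure for this comparison, so there is none to reproduce. The two calculations below show how far a crude ratio can move. The true effect of hospital care and the strength of selection are assumed throughout, because the protocol states neither.

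**1. Two severity groups, all inputs assumed.** Treatment failure is 30% in more severe and 10% in less severe children, 20% of refusers are more severe, and hospital care has a true RR of 0.75. With p the share of more severe children among acceptors:

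crude RR = 0.75 × [0.30p + 0.10(1 − p)] / [0.30 × 0.20 + 0.10 × 0.80], with denominator 0.14.

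The last column is the ratio of acceptance rates (more severe to less severe) that each row implies. It uses 12.5% overall acceptance, the midpoint of the 10% and 15% in the Sample size section. For p = 50%, acceptance is 0.0625/(0.0625 + 0.175) = 0.263 in more severe and 0.0625/(0.0625 + 0.70) = 0.082 in less severe children, a ratio of 3.2.

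| p | Acceptor risk before care effect | Crude RR if care has no effect | Crude RR if true RR is 0.75 | Implied acceptance ratio |
|---|---|---|---|---|
| 10% | 0.12 | 0.86 | 0.64 | 0.5 |
| 30% | 0.16 | 1.14 | 0.86 | 1.6 |
| 40% | 0.18 | 1.29 | 0.96 | 2.3 |
| 50% | 0.20 | 1.43 | 1.07 | 3.2 |
| 60% | 0.22 | 1.57 | 1.18 | 4.5 |

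The first row is the case where acceptors are the less severe group. The benefit is then exaggerated.

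**2. Hypoxaemia as the confounder, partly anchored on the protocol.** From the protocol come the risk ratio of 4.3, the total of 4160 children and the 12.5% acceptance midpoint. The assumptions are 25% hypoxaemic (the Introduction gives 16% to 39% for acutely ill children in the community), a threefold acceptance ratio, a base risk of 5% and a true RR of 0.80.

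- Acceptance is 0.125/(0.75 + 0.25 × 3) = 8.3% without hypoxaemia and 25% with it.
- With hypoxaemia: 260 acceptors at risk 0.172 and 780 refusers at 0.215. Without: 260 acceptors at 0.04 and 2860 refusers at 0.05.
- Crude acceptor risk is (44.72 + 10.4)/520 = 10.6%.
- Crude refuser risk is (167.7 + 143)/3640 = 8.5%.
- The crude RR is 1.24. The Mantel-Haenszel RR stratified by hypoxaemia is 0.80, the value put in.

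**3. How much selection reverses the sign.** With risk ratio 4.3, prevalence 16% to 39% and acceptance 10% to 15%, the crude RR passes 1 when hypoxaemic children's families accept at least this many times as often:

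- 1.3 to 1.4 times if the true RR is 0.9;
- 1.7 to 1.9 times if it is 0.8;
- 2.4 to 2.9 times if it is 0.7.

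The 4.3 is for mortality, which is not one of the three outcomes named for this contrast. With a severity risk ratio of 2 and a true RR of 0.8, the threshold rises to 3.1 to 3.7 times.

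**The case against.** The strongest reply is that the chi-square and t-test sentence is never tied to the secondary objective. It follows a sentence about baseline characteristics by arm, and covariates for an observational secondary analysis are often left to an analysis plan, which is not shown here. It stands that applying those tests to this contrast is a reading of general wording. But they are the only outcome tests stated, and adjustment is expressly described for acceptance alone, so a team following the text would produce the crude comparison.

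Several stronger readings are tempting, and the protocol does not support them:

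- *Sicker children are expected to accept more often.* The predictors are listed without direction. The oximeter reading is used to persuade parents only in intervention clusters, and the Introduction names distance and lack of money as barriers.
- *Outcomes that refusers cannot have are assigned to this contrast.* The general list reads "Secondary outcomes include duration of oxygen therapy, treatment failure, duration of hospital stay", but the objective itself names only treatment completion, treatment failure and hypoxaemia.
- *The investigators intend to base management conclusions on it.* Limitations speaks of a need to "correlate recovery rates in those who accepted hospital referral versus those who stayed home on oral amoxicillin", as follow-on work conditional on oximetry having influenced care-seeking.
- *The objective contradicts the intention-to-treat statement.* That statement governs the primary analysis of each outcome. An additional observational contrast can sit beside it if it is labelled as such.

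**Conclusion.** The point holds in limited form. As written, the secondary objective would be met by a comparison confounded by severity and access, and the protocol itself lists the variables involved. The size is unknown. With a true RR of 0.75 and the assumed failure risks, the crude RR is 0.86 at a 30% against 20% split, and 0.96 to 1.18 at 40% to 60% against 20%. It falls to 0.64 if selection runs the other way at 10% against 20%.

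A reader might infer that a benefit of hospital care will appear as harm. That is one possible result, requiring fairly strong selection by severity, and it is not a prediction. The primary outcome, referral acceptance by arm, is not affected.

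**What to change.** **Acceptors versus refusers.** State that this comparison is observational. Estimate it with a regression that accounts for clustering and adjusts for the listed candidate predictors of acceptance and the danger signs assessed at screening in both arms. Include the health worker's SpO2 reading within intervention clusters only. State that residual confounding remains, because health workers in control clusters do not measure SpO2.

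**By randomised arm.** Report treatment failure and day-7 and day-14 status by allocated arm, in line with the Data analysis section. Restrict this analysis, or add a version restricted, to children meeting the clinical-signs definition common to both arms. Children with hypoxaemia alone can be enrolled only in intervention clusters, so an analysis of all enrolled children would compare differently selected groups.

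**Cost.** The change is to analysis wording. The predictors are already planned and the danger signs are already assessed. The data forms are in a supplement that is not shown, so the team should confirm that each item is recorded. The arm comparison will have limited power for clinical outcomes, and the adjusted observational comparison will still not be free of confounding.
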